### Other data

#### *Parent reported*

Parents will provide basic socio-demographic information about themselves and their child at baseline, and will include the following demographic details: child’s eligibility for free school meals, post code to link to the index of multiple deprivation, the number of children living in the household, housing tenure (rented or not), and the highest level of qualification of the parent(s) or carer(s).

#### *School reported*

We will gather school level data on the percentage of children eligible for school meals at recruitment and the index of multiple deprivation at lower super output area as a proxy for the school catchment area according to the school’s postcode [30]. We will also obtain information from schools about the type and level of emotional enrichment programmes (e.g. Socio-emotional aspects of learning, Thrive) being delivered in school, and how much other outside behavioural support they receive.

#### *Nested qualitative study within process evaluation*

Sampling within the process evaluation will be purposive [35,36] to facilitate data collection of the views and experiences of participants, who can comment on the delivery, uptake and use of TCM strategies, appropriate to each phase of the trial. All intervention teachers in the trial will be invited to take part in focus groups. Sampling of Head-teachers and SENCos will reflect the aims of each trial phase.

##### Course experience and research processes

The aims of the process evaluation for the first cohort are to elicit a fuller understanding of the experiences of the course, course delivery and research process. All intervention group teachers (n = 10) will be invited to join a focus group after the course finishes. All head teachers from intervention group schools will be invited to take part in a telephone interviews (n = 10). Head teachers from control group schools (n = 5) will also be invited to take part in a telephone interview to elicit their views on the research processes.

##### Teacher learning and use of TCM strategies

In cohorts 2 and 3, all teachers in the intervention groups (15 in each year) will be invited to join a focus group aiming to elicit views and experiences of the learning, uptake and use of TCM strategies in the classroom. For teachers in their follow up year (i.e. second and third years of participation) all teachers from the previous year’s course will be invited to join a focus group to elicit views on maintenance of the use of TCM techniques in the classroom.

##### Impacts of course

In each of second and third years of participation, we plan to conduct interviews with up to 15 head teachers and 15 SENCos from the intervention schools In this phase we will aim to achieve a diversity of head-teachers and SENCos from a range of schools [36].

Although not the only issue affecting sample size in qualitative research, a guiding principle includes the concept of saturation [37,38]. Our sample size takes account of current guidance on optimising sample size in qualitative research.

### Statistical analysis

#### *Analysis of effectiveness*

All comparisons between trial arms will use the intention to treat principle where schools and participating pupils are analysed according to the arm to which they were randomised. Random effects linear regression models [39] will be fitted to compare means for continuous outcomes (including the primary outcome or SDQ total difficulties score) between the trial arms allowing for the correlation between outcomes of children from the same school specifying school effects as random. The method of marginal models using Generalised Estimating Equations with information sandwich (“robust”) estimates of variance and assuming an exchangeable correlation structure within school clusters [40] will be used to compare binary outcomes (e.g. borderline/abnormal versus normal status on the SDQ) between the trial arms, also allowing for clustering. A test of interaction will be implemented for each outcome to investigate whether the intervention effect differs across the three time points (T1, T2, T3).

Unadjusted analyses and analyses adjusted for important prognostic factors at the pupil level (e.g. child gender, year group and baseline SDQ score), cohort of recruitment and the school level (level of deprivation, urban versus rural status and whether involved in other emotional enrichment programmes) will be implemented. In a secondary analysis, interaction terms will be included to investigate possible differences in intervention effect (on the primary outcome SDQ score only) between pre-defined subgroups based on school and individual deprivation, low versus high baseline SDQ scores, length of teacher experience and year group. These sub-group analyses have been selected for a number of reasons. First, children experiencing socio-economic deprivation may benefit more than their more privileged peers. Second, previous work suggests that children with higher levels of difficulties experience the most benefit [10]. Third, teachers in our Feasibility Study suggest that newly-qualified teachers would gain the most from the course, and finally, there is a common belief that these interventions will have the biggest impact on younger children. The latter belief has focused research on very young children and this would be the only study to investigate TCM in children aged over seven years. P-values of 0.01 and less will be interpreted as providing evidence for interaction effects. Although the power to detect moderate subgroup interactions will be low, we are primarily interested in investigating the possibility of large quantitative interactions and not qualitative interactions where the direction of intervention effect differs between sub-groups. Demographic and baseline characteristics at the school and pupil level will be summarised using means and standard deviations (or medians and inter-quartile ranges) for quantitative characteristics and percentages for categorical characteristics.

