**Methods/Design:**

Cluster randomised controlled trial (RCT) of the Incredible Years teacher classroom management (TCM) course with combined economic and process evaluations.

One teacher of children aged 4–9 years, from 80 schools in the South West Peninsula will be randomised to attend the TCM (intervention arm) or to “teach as normal” (control arm). The primary outcome measure will be the total difficulties score from the Strengths and Difficulties Questionnaire (SDQ) completed by the current class teachers prior to randomisation, and at 9, 18 and 30 months follow-up, supplemented by parent SDQs. Secondary measures include academic attainment (teacher report supplemented by direct measurement in a sub-sample), children’s enjoyment of school, and teacher reports of their professional self-efficacy, and levels of burn out and stress, supplemented by structured observations of teachers classroom management skills in a subsample. Cost data for the economic evaluation will be based on parental reports of services accessed. Cost-effectiveness, using the SDQ as the measure of effect, will be examined over the period of the RCT and over the longer term using decision analytic modelling. The process evaluation will use quantitative and qualitative approaches to assess fidelity to model, as well as explore Head teacher and teachers’ experiences of TCM and investigate school factors that influence the translation of skills learnt to practice.

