### The intervention: the teacher classroom management programme

The intervention being evaluated is the IY Teacher Classroom Management (TCM) programme [14]. TCM draws on cognitive social learning theory, particularly Patterson’s theories [15] about how coercive cycles of interaction between adults and children reinforce unwanted behaviour patterns, Bandura’s ideas [16] about the importance of modelling and self-efficacy, and Piaget’s developmental interactive learning methods [17]. In addition, it also incorporates strategies for challenging angry, negative, and depressive internal dialogue in adults whilst interacting with children, drawn from cognitive behavioural approaches. TCM is delivered to groups of ten teachers, and involves six whole-day sessions spread over a period of six months. It is delivered in a collaborative style with group leaders encouraging all to share their experience and expertise and to value that of others. The explicit goals are to: a) enhance teacher classroom management skills and to improve teacher-student relationships; b) assist teachers to develop effective group and individual behaviour plans to enable proactive rather than reactive classroom management; c) encourage teachers to adopt and promote social and emotional regulation skills; and d) encourage teachers to strengthen positive teacher-parent relationships with all parents.

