## Methods/Design

### Aims/objectives

· To evaluate whether TCM improves socio-emotional well-being among children as measured by the teacher completed Strengths and Difficulties Questionnaire (SDQ) cross-validated with direct observation, parental SDQ and child report on How I Feel About My School where available.

· To evaluate whether TCM improves academic attainment as measured by teacher assessment of pupil progress (APP) cross-validated with standardised assessments and SATS where available.

· To evaluate whether any improvements in well-being and attainment are sustained over the next two academic years.

· To evaluate whether TCM reduces ‘burn out’ and improves self-efficacy and well-being among teachers using the Maslach Burn Out Inventory, the Teacher Self-Efficacy Questionnaire and the Everyday Feelings Questionnaire.

· To evaluate whether TCM improves teacher’s classroom management skills using the behavioural management strategies reported by teachers in the Teacher Satisfaction Questionnaire.

· To use qualitative methods to investigate how teachers apply the strategies suggested by TCM in the classroom and any factors that may influence this process, including: year group taught, school climate and additional support and advice available to them.

· To evaluate both the utility of TCM to teachers in their practice one year after attending the course and how TCM is related to additional sources of behavioural support and school context.

· To evaluate the cost and cost-effectiveness of TCM compared to teaching as usual at final follow-up.

· To extrapolate the results from the randomised controlled trial (RCT) into young adulthood using decision analytic modelling and published data to explore the longer-term cost and cost-effectiveness implications of TCM compared to teaching as usual and to model potential cost savings in the longer term.

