### Design

#### *Cluster randomised controlled trial*

The core of the study will be a pragmatic cluster randomised controlled trial with one teacher and their pupils per primary school (cluster) allocated to TCM training or teaching as usual (TAU). The recruitment plan is dictated by the school academic year and the duration of the intervention (six months), which means that the TCM course can only run once per academic year. Eighty schools will be recruited over three year; 15 in Cohort 1, 30 in Cohort 2 and 35 in Cohort 3.

Each school will participate in the trial for three academic years. Child and teacher outcomes will be assessed at the beginning and end of the first academic year (T0 and T1). At the end of the first academic year, teachers and children will separate; the study children will have new teachers in each follow up year (T2 and T3), who will complete the child well-being measures even if a child moves school. The study teachers will also be working with a new class of children, which allows us to offer the control teachers TCM in the second year of participation (i.e. *after* recruitment) as an incentive for participation. Child outcomes will be measured in both follow-up years (T2 and T3) as part of the follow up trial design. Schools sometimes move teachers around year groups for school improvement purposes, so the situation may arise when a teacher and children participating in the trial may come back into contact with each other during the follow up period. Control teachers will be offered access to TCM in the second year of participation in the trial, so contact between control children and control teachers would serve to reduce any differences between the arms of the trial, while contact in the second and third years of participation between TCM children and TCM teachers may increase the differences between arms by effectively giving these children a double dose of the intervention. We will explain verbally and in writing to head teachers at recruitment why it is important to avoid a reunion between the teacher and their baseline class during follow-up and we will monitor schools closely to record if this does happen. To prevent contamination and to reflect how the intervention might be rolled out in ‘real life’, the unit of allocation is the school; one teacher per school will participate.

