### Randomisation and concealment

Schools will be randomised to intervention (TCM course) or control (Teaching As Usual, TAU) through a password protected trial website that will be set up and maintained by the UKCRC accredited Peninsula Clinical Trials Unit. Randomisation will be stratified by the following: *level of**deprivation at**school level* (below or above 19% of pupil’s eligible for free school meals); *city/non city**location* (Plymouth/Exeter/Torbay versus other addresses); and *school year* (Key Stage 1 or Foundation and Years 1–2 versus Key Stage 2 or Years 3 and 4). To ensure concealment, all schools within each cohort of recruitment will be randomised simultaneously after the baseline measures have been completed.

We will be unable to blind the staff in schools as to which group they are allocated to. Researchers undertaking the observations of teachers will be external to the core research team and will be kept blind to group allocation at all times, although it is possible that teachers may inadvertently disclose this information to them. We will ask these researchers to guess which groups the teachers that they observed were in at the end of their follow up observations to check if blinding was maintained and to tell us if a teacher informed them about their allocation. Baseline measures will be completed before randomisation and therefore all parties will be blind to allocation at this point. Parents and children are unlikely to be aware of whether their child’s teacher has completed the TCM course and the follow-up measures, with the exception of the service-related interviews completed by parents on a sub-sample and the child measures, are questionnaires that are completed independently and thus difficult for the core team of researchers to influence should they become aware in their liaisons with school about allocation. In addition, the teacher-completed follow-up measures in the second and third year of each school’s participation in the study (T2 and T3) will be completed by a teacher that did not access the intervention, although they are likely to know whether their colleague did or not.

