### Assessment and follow up

The trial will start two weeks into the new school year in September. Parents will have two weeks to opt themselves and their child out of the trial. Baseline assessments (T0) will be completed by the October half term holiday. The measures will be completed by the child (on themselves), their parent (on themselves, their child and their child’s use of services) and the class teacher (on the children and themselves). Direct observations in the classroom will take place with a subsample during this time. Following randomisation, the intervention group teachers will then start the TCM course in early November. Literacy/numeracy assessments with a subsample of children will take place in the February/March.

The first follow-up assessment, identical to T0, will be completed in May/June of that first academic year (T1 or nine months post baseline), with the classroom observations completed by researchers blind to allocation.

Each school participates in the trial for three academic years. Only the measures relating to the children (including SDQs completed by their subsequent teachers in the two follow up years) contribute to trial follow-up data at T2 (18 months post baseline) and T3 (30 months post baseline). The teachers will complete the measures relating to themselves to assess the impact of TCM on professional functioning in the longer term, but at T2 and T3 these will no longer contribute to trial outcome data as described earlier. As the recruitment is rolled out over three years, the assessment of different cohorts will be carried out simultaneously within the same school year.

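### For the teacher-rated SDQ, the arm-by-time test over T1, T2 and T3 is confounded with a change of rater, so read alone it cannot show whether an effect fades

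*Protocol article*

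**What the plan says.** The Abstract defines the primary outcome as the SDQ total difficulties score "completed by the current class teachers prior to randomisation, and at 9, 18 and 30 months follow-up, supplemented by parent SDQs". The rater is thus whoever teaches the child at the time.

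- **T0 and T1.** Under Assessment and follow up: "The first follow-up assessment, identical to T0, will be completed in May/June of that first academic year". The children are still with the study teacher, so that teacher rates both. Under Randomisation and concealment: "We will be unable to blind the staff in schools as to which group they are allocated to".
- **T2 and T3.** Under Cluster randomised controlled trial: "the study children will have new teachers in each follow up year (T2 and T3), who will complete the child well-being measures". Randomisation and concealment adds that the teacher measures in those years "will be completed by a teacher that did not access the intervention", and that these teachers will probably know whether their colleague did.
- **Intervention.** The course "incorporates strategies for challenging angry, negative, and depressive internal dialogue in adults whilst interacting with children", among other components.
- **Analysis.** Analysis of effectiveness: "A test of interaction will be implemented for each outcome to investigate whether the intervention effect differs across the three time points".
- **Objective.** Aims/objectives: "To evaluate whether any improvements in well-being and attainment are sustained over the next two academic years".

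Parents complete the SDQ at all four time points. The teacher SDQ is to be cross-validated against the parent SDQ in general terms, but the article does not connect this to the time interaction. The change of rater is mentioned in the account of blinding and not in the analysis section.

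**The concern.** Both arms change rater after T1, and a change common to both arms would cancel in the arm difference. The difficulty is that the change is not the same in the two arms. Only the TCM arm moves from a rater who attended the course to one who did not. The course deals with how teachers think about and respond to children, so it could alter how a teacher scores the same behaviour as well as the behaviour itself. Knowledge of having been allocated to TCM could do so too.

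Each teacher-SDQ arm difference is the true effect plus any arm-specific shift in rating. Adjustment for the baseline SDQ does not remove a shift that arises after T0, because T0 was rated before randomisation and training.

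At stake is the objective on sustained improvement. A constant true effect with a favourable rating shift at T1 would look like an effect that wanes. No true effect with the same shift would look like a short-term benefit that is later lost. An unfavourable shift, for example because training makes a teacher notice more difficulties, could hide an early effect or make it seem to grow.

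**Working it through.** **Inputs from Proposed sample size.** 40 schools per arm, 19 children per school at T3, ICC 0.15, target effect 0.3 SD, 5% level, stated power 85%.

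**Inputs that are assumptions.** The correlation rho of the arm differences between years, taken as exchangeable (0.5, range 0.3 to 0.7); the arm-specific rating shift b at T1 (0.1, 0.2 or 0.3 SD), with none at T2 and T3; a constant true effect; the same number of children at each time point.

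**Step 1: reproduce the stated power.** VIF = 1 + (19 - 1) x 0.15 = 3.7. Effective n = 760/3.7 = 205.4 per arm. Power for 0.3 SD, two-sided 5%, is 85.9% by the normal approximation and 85.1% with a t distribution on 78 df. The stated 85% is reproduced.

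**Step 2: standard error at one time point.** Variance of a school mean = 0.15 + 0.85/19 = 0.1947. Variance of the arm difference = 2 x 0.1947/40 = 0.00974, so SE = 0.0987 SD. This equals sqrt(2/205.4).

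**Step 3: what the test can distinguish.** Compare pairs of situations:

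| Situation | True effect T1/T2/T3 | Shift at T1 | Expected contrast T1/T2/T3 |
|---|---|---|---|
| A | 0.3 / 0 / 0 | 0 | 0.3 / 0 / 0 |
| B | 0 / 0 / 0 | 0.3 | 0.3 / 0 / 0 |
| C | 0.15 / 0.15 / 0.15 | 0.15 | 0.3 / 0.15 / 0.15 |
| D | 0.3 / 0.15 / 0.15 | 0 | 0.3 / 0.15 / 0.15 |

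A and B have the same expected contrasts, and so do C and D. At rho = 0.5 the test rejects in 89% of trials under A and under B, and in 33% under C and under D. More data would not separate the members of a pair.

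**Step 4: rejection rate when the true effect is constant.** For the 2-df Wald test of equal effects, with T1 shifted by b, the noncentrality is lambda = (2/3) x b^2 / [SE^2 x (1 - rho)]. For b = 0.2 and rho = 0.5: (2/3) x 0.04 / (0.00974 x 0.5) = 5.48. The rejection rate is the probability that a noncentral chi-square on 2 df exceeds 5.99.

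| Shift b (SD) | rho = 0.3 | rho = 0.5 | rho = 0.7 |
|---|---|---|---|
| 0.1 | 13% | 17% | 25% |
| 0.2 | 41% | 54% | 78% |
| 0.3 | 76% | 89% | 99% |

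The correct rate would be 5%. If the 0.01 threshold that the article gives with its subgroup interactions were applied here, the rates at rho = 0.5 would be 5.5%, 31% and 74%, against a correct 1%.

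**The case against.** The strongest reply is that the article contains no wrong rule. It says that an interaction will be tested, not that a significant result will be called fading. The sustained-effect objective does not name the interaction test, and it can be answered from the T2 and T3 differences. A reader might infer that the protocol commits itself to reading a significant interaction as waning; the text does not say so. Nevertheless, the article offers no other reading of this test, and it is the only stated analysis that compares effects over time.

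Second, the safeguard is largely there. The test applies to every outcome, so the parent-SDQ interaction is already included, and parents are expected to be mostly unaware of allocation. This stands. What is missing is the link between the two analyses. The classroom observations cannot fill the gap, since they cover 20 classrooms, compare T0 with T1 and focus on the teacher.

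Third, the shift is hypothetical. The earlier Limerick trial, as the article reports it, found changed teacher behaviour but little evidence of change in teacher-rated child well-being. That trial had 22 teachers, so it is weak evidence, but it lends no support to a large shift. This limits what can be said about size and not the confounding itself.

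Fourth, a reader might infer that rater bias disappears after T1. The documents do not support that, because the later raters are also unblinded. Bias may be smaller or different, not necessarily absent. In some schools the study teacher and the baseline class may also be reunited, which the team plans to record.

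Finally, a reader might want parent ratings to confirm any fading before it is believed. That goes too far. Parents report from home and TCM acts in the classroom, so a real classroom effect could fade without a parent-rated trace.

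**Conclusion.** The point holds as one of confounding. For the teacher SDQ, the contrast of T1 with T2 and T3 combines any change in the true effect with any change in arm-specific rating, and the planned test sees only their sum. It could therefore mislead on the sustained-effect objective if read alone. Under the assumptions set out in the working, a shift of one third of the target effect (0.1 SD) raises the rejection rate from 5% to 17%, and a shift equal to the whole target effect raises it to 89%. These figures are illustrations. The document does not say that a shift exists, which way it would go or how large it would be. The sample size and the stated power are unaffected. The change is worth making because it costs almost nothing and bears on a named objective.

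**What to change.** In Analysis of effectiveness:

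1. Base the sustained-effect conclusion for the teacher SDQ on the arm differences at T2 and at T3, where the raters are of the same kind in both arms.
2. Report the T1 teacher-SDQ estimate separately, described as rated by the unblinded study teacher.
3. Keep the teacher-SDQ interaction over T1 to T3, but state that a difference between T1 and the later time points cannot by itself be attributed to fading.
4. Name the parent-SDQ interaction over T1 to T3 as the companion analysis with a constant kind of rater, and present the two side by side. Do not make agreement between them a required condition.

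The cost is a few sentences, since all the data are already to be collected. The downsides are that the parent analysis may be less precise if fewer parents respond, and that it measures behaviour from the home perspective. It informs the reading of the teacher result but does not settle it.
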